### Specific aims

The primary aim of this pragmatic comparative effectiveness study is to compare pain and disability of active duty military personnel with LBP who are treated with chiropractic care and usual medical care compared with those treated with usual medical care alone. We hypothesize that those allocated to receive both chiropractic care and usual medical care will show greater reduction in pain and disability than those receiving usual medical care alone.

Secondary aims explore the effects of adding chiropractic care to usual medical care on healthcare utilization, medication use, and quality of life.

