#### Primary outcome measures

The co-primary outcome measures are the Numeric Rating Scale (NRS) for average pain intensity during the past week and the Roland-Morris Disability Questionnaire (RMDQ). The NRS has excellent metric properties, is commonly used in RCTs studying LBP [34, 35], and has been demonstrated as a valid and reliable measure [36]. Participants are asked to rate their average level of LBP during the past week on an ordinal 11-box scale (0 = no LBP; 10 = worst possible LBP). The RMDQ is a reliable and valid LBP-related disability assessment instrument commonly used in clinical research [37, 38]. Containing 24 questions, it is considered sensitive to disability-related changes in patients with LBP [39–41].

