#### Primary data analysis and sample size

The co-primary outcome variables (RMDQ and the NRS for LBP intensity) will be modeled with linear mixed effects regression over baseline and weeks 2, 4, 6, and 12. We will assume group means are the same at baseline, and include terms in the model for time (as a categorical variable), site, site-by-group, time-by-group, and site-by-time-by-group interactions, and the variables in the minimization algorithm. The covariance structure will be chosen by comparing the maximized log-likelihoods and the Bayesian information criteria for several covariance pattern models against the unstructured covariance. Diagnostics of the conditional predicted values and conditional residuals will be used to assess the assumption of normality and fit for each model.

The main results will be based on the final models for the co-primary outcome variables at the end of the active care phase (6 weeks). If the site-by-time-by-group interaction is significant at the 0.05 level, results will be reported by site. A *p*-value ≤ 0.025 will be used to determine if between group differences are statistically significant.

Because the patient populations at the three sites are different, we calculated a sample size of 106 per group for each site to provide adequate power to detect clinically important differences between groups at each site. The sample size estimates were obtained using a significance level of 0.025 to account for 2 primary outcome variables. The estimates of standard deviation (5.4 for the RMDQ and 2.0 for the NRS for average pain intensity over the past week) come from our pilot study [28]. This provides 80 % power to detect a 2.4 between group difference on the RMDQ and 92 % power to detect a 1.2 difference on the NRS. In the pilot study, there was 13 % and 11 % missing data in the UMC plus chiropractic care group at the week 2 and 4 assessment periods, respectively, but 39 % and 37 % in the UMC alone group. We increased the sample size to 125 per group at each site, assuming we would be able to keep our loss to follow-up at the week 6 endpoint at or below 15 %, due to the implementation of intensive follow-up procedures.

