Two approaches to sensitivity analyses will be used to examine the possible effects of missing data on the results obtained from using all observed data for the co-primary outcome variables. Prior to conducting the sensitivity analyses, baseline variables that are predictive of missing outcomes will be identified with logistic regression models. The first approach will be under the assumption that data are missing at random and will use the Markov chain Monte Carlo method to impute missing values for each of the primary outcome variables based on the final mixed model covariates, the observed outcome variable at baseline and weeks 2, 3, 6, and 12, and the baseline variables predictive of missing data. The resulting datasets for each of 20 imputations will be analyzed with the linear mixed effects models that are fit with all observed data and the results will be combined. The second approach will be under the assumption that data are missing not at random. It will follow the pattern mixture approach described by Carpenter and Kenward [51] by first imputing missing values as described above for the missing at random approach and then for each participant in each treatment group for each imputation. The imputed observation will be decreased by different amounts representing different patterns of responses. The resulting datasets for each pattern will be analyzed and the estimates combined as described above. If results differ between the analysis of the observed data and that based on imputed full datasets under different missingness assumptions, multiple sets of results will be reported.

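### The missing-not-at-random analysis only lowers imputed scores, so it never examines missing participants who did worse than predicted, in either arm

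*Protocol article*

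**What the plan says.** All references are to the protocol article.

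- **Primary data analysis and sample size, sensitivity analyses.** There are two approaches. The first imputes under missing at random, with 20 imputations. The second is a pattern-mixture analysis that starts from the same imputations and then alters them: "The imputed observation will be decreased by different amounts representing different patterns of responses". The sentence before this ends with "then for each participant in each treatment group for each imputation" and has no verb for that clause. The sizes of the shifts are not given, and neither is whether they may differ between arms. Additional sets of results are to be reported if the imputed analyses disagree with the observed-data analysis.
- **Primary outcome measures.** The NRS is anchored "0 = no LBP; 10 = worst possible LBP". The RMDQ is described as having 24 questions, and its scoring direction is not stated.
- **Specific aims.** The chiropractic group is expected to be the one that "will show greater reduction in pain and disability than those receiving usual medical care alone". This makes a lower score the better one on both scales.
- **Primary data analysis and sample size, sample size paragraph.** The pilot had "13 % and 11 % missing data in the UMC plus chiropractic care group" at weeks 2 and 4, against 39% and 37% with UMC alone. For this trial the authors expect to "keep our loss to follow-up at the week 6 endpoint at or below 15" per cent.

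**The concern.** A missing-not-at-random analysis should show how far the unseen outcomes would have to depart from the imputation model before the conclusion changes. Here the departure is fixed in one direction. Subtracting from a score on which lower is better supposes that the people who did not report were better off than predicted. Nowhere does the article provide for the opposite.

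The opposite is a realistic possibility. The Study limitations section accepts that participants and treating clinicians cannot be blinded, and pilot missingness depended strongly on arm, so response and dropout may well be linked. If chiropractic participants who were not improving stopped reporting, their imputed scores would be too low, and only an upward shift in that arm represents this directly.

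The reporting rule adds to the problem. Extra results appear only when analyses disagree, and a direction that is never run cannot produce a disagreement.

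**Working it through.** **Plan's own figure.** The one design number tied to missingness reproduces: 106 / (1 − 0.15) = 124.7, which rounds up to the stated 125 per group per site.

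**Inputs from the article.** Design differences are 2.4 (RMDQ) and 1.2 (NRS). SDs are 5.4 and 2.0. There are 106 evaluable per group at each site. The significance level is 0.025, taken here as two-sided. Missingness is 15% in each arm as planned, or 11% chiropractic and 37% UMC as at pilot week 4.

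**Assumed.** The article gives no shift sizes, so all those used below are illustrations.

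**Formula.** Let m be the fraction missing in an arm and d the amount added to its imputed values. The change in the chiropractic-minus-UMC difference is

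m_C × d_C − m_U × d_U.

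A negative difference favours chiropractic.

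**RMDQ, starting from −2.40, shift of 2.4 points**

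| Scenario | Reachable by decreases? | 15% / 15% | 11% / 37% |
|---|---|---|---|
| Both arms decreased equally | yes | −2.40 | −1.78 |
| UMC only decreased | if arms may differ | −2.04 | −1.51 |
| Chiropractic only decreased | if arms may differ | −2.76 | −2.66 |
| Chiropractic only increased | no | −2.04 | −2.14 |
| Both arms increased equally | no | −2.40 | −3.02 |

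Example, equal decrease at 11% / 37%: −2.40 + 0.11 × (−2.4) − 0.37 × (−2.4) = −2.40 − 0.264 + 0.888 = −1.78.

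The NRS behaves in the same way. From −1.20 with a 1.2-point shift at 11% / 37%, an equal decrease gives −0.89, a chiropractic-only increase −1.07 and an equal increase −1.51.

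**Size of the omitted case at 15% missing**

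- RMDQ, chiropractic dropouts 3 points worse: 0.15 × 3 = 0.45, leaving 2.4 − 0.45 = 1.95.
- NRS, chiropractic dropouts 2 points worse: 0.15 × 2 = 0.30, leaving 1.2 − 0.30 = 0.90.

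**One-site significance threshold.** This is z × SD × √(2/106), with z = 2.241 and the standard error held fixed.

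- RMDQ: 2.241 × 5.4 × 0.1374 = 1.66, a margin of 2.4 − 1.66 = 0.74.
- NRS: 2.241 × 2.0 × 0.1374 = 0.62, a margin of 1.2 − 0.62 = 0.58.

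**Tipping points (unrounded margin divided by fraction missing)**

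- Shift in one arm only, 15% missing: 0.737 / 0.15 = 4.9 RMDQ; 0.584 / 0.15 = 3.9 NRS. These apply equally to a chiropractic increase or a UMC decrease.
- Chiropractic-only increase, 11% missing: 6.7 RMDQ; 5.3 NRS.
- UMC-only decrease, 37% missing: 2.0 RMDQ; 1.6 NRS.

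**The case against.** The strongest reply is that only the contrast between arms matters, and decreases can move that contrast against chiropractic. This is correct. At 15% in each arm, lowering UMC dropouts by 2.4 RMDQ points gives −2.04, exactly what raising chiropractic dropouts by 2.4 gives. At the pilot's week-4 rates even an equal decrease takes the difference to −1.78, while an equal increase would flatter chiropractic (−3.02).

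A reader might therefore be tempted to infer that the stated analysis cannot threaten a chiropractic benefit, or that worse-than-predicted dropouts are the one case that could overturn it. The document supports neither inference. The first would need a common decrement and equal missingness, and the article does not commit to a common decrement. The second is refuted by the arithmetic above.

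It can also be said that shift sizes, grids and arm-specific amounts belong in an analysis plan that is not shown, that the passage is condensed and rests on a cited method, and that a decrease may have been meant as less improvement. The sizes are indeed no finding. The direction is different, because the article states it and applies it to the imputed observation itself.

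Nor is the UMC-decrease route a full substitute. It needs arm-specific amounts that the text does not promise, and the scale floor limits it: a UMC dropout imputed below 3.9 on the NRS cannot be lowered by 3.9 without leaving the 0–10 range.

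**Conclusion.** The point holds as a badly fixed direction in a sensitivity analysis. As written, no scenario has missing participants doing worse than missing at random predicts, so non-response among chiropractic dropouts is not examined directly, and dependence of the shift on arm is left unstated. With equal missingness, an equal decrease tests nothing about the group difference.

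The likely size is modest. The illustrative 0.45 RMDQ and 0.30 NRS are 19% and 25% of the design differences, and what remains (1.95 and 0.90) stays above the one-site thresholds of 1.66 and 0.62. Losing significance at one site would take a chiropractic-only worsening of about 4.9 RMDQ or 3.9 NRS points at 15% missing.

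These figures assume that the design effects and SDs are observed, that there are 106 per group at one site, and that the standard error does not change with the shift. The shift sizes are assumptions, and the RMDQ direction is inferred from the Specific aims. The primary estimate, the 0.025 criterion and the sample size are unaffected. Severity is moderate; this is not a must-fix.

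**What to change.** In the sensitivity-analysis paragraph, replace the one-way decrease with shifts in both directions, by amounts that may differ between arms. Name at least these two scenarios:

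1. Chiropractic imputed values increased, with UMC left at missing at random.
2. UMC imputed values decreased, with chiropractic left at missing at random.

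For each co-primary outcome, run the shifts over a range and report the shift at which significance is lost, whether or not the results disagree with the observed-data analysis. Note where shifted values leave the scale range: 0–10 for the NRS, and 0–24 for the RMDQ if each of its 24 questions scores one point. Complete the unfinished clause so that it says who is shifted.

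The cost is a short text change and a few more runs on the 20 imputed datasets already planned. No new data are needed.

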#### Secondary data analysis

The continuous secondary outcome variables will be analyzed with linear mixed effects regression as described above, but *p*-values ≤ 0.05 will be used to determine if between group differences are significant. The ordinal categorical variable representing the number of days that participants reported using medications for LBP over the past week will be analyzed over baseline and weeks 2, 3, 6, and 12 with a proportional odds model. Generalized estimating equations using all observed data with a working covariance structure will be used to fit the model.

### Protocol fidelity and quality assurance

#### Protocol fidelity

We are carefully tracking intervention and protocol adherence. Using the Armed Forces Health Longitudinal Technology Application, or patient electronic medical record, we are tracking all care received for LBP during the 3-month study duration. This includes both UMC visits, as well as chiropractic visits. Instances where participants who are allocated to receive UMC only but do receive chiropractic care during the 6 weeks of active care, as well as participants who are allocated to receive chiropractic care but do not will be classified as unanticipated events and documented in STaRS.

#### Internal quality assurance process

The lead PM conducts an internal quality assurance audit at each site on a quarterly basis for the purpose of maintaining data integrity, ensuring study protocol fidelity, and standardizing study operating procedures across all three sites. During the audit, the lead PM reviews regulatory documentation and informed consent documents. Electronic data are verified by comparing the paper source documents to the data entered in STaRS. Any errors discovered during the quarterly audits are documented, corrected by the site PM, and reported to the site PI, collaborating investigators, and appropriate regulatory bodies, if applicable.

During these site visits, the lead PM also meets with site PMs, PIs, DCs, and/or clinic command to facilitate communication about overall study status and discuss study timelines, as well as address site concerns or barriers interfering with study conduct. Information gathered during the site visits is conveyed to study co-investigators. In addition, the PCCR PI has a monthly conference call with study personnel at each clinical site to monitor study progress.

### Study event monitoring and reporting

#### Adverse events

We have defined an adverse event as any untoward medical occurrence presenting during the active study period (6 weeks) that may or may not have a causal relationship with study procedures [52]. A serious adverse event is defined as an event resulting in a condition considered as life-threatening, a congenital anomaly or birth defect, in-patient hospitalization, disability, permanent damage, death, or an occurrence that requires intervention to prevent death or significant disability. Adverse event information is being collected via 1) direct report to PM and/or 2) self-report during online assessments.

Participants are encouraged to contact the PM if there are any unplanned hospitalizations/procedures or for any other health-related events whether or not the participant considers them related to the study. When participants report adverse event information directly to a PM, the PM enters the adverse event information into STaRS, which generates an auto-notification message to the lead PM, designated trial clinician, and PI. Participants are also being prompted to answer questions about adverse events during the week 2, 4, and 6 online assessments. The lead PM and the central trial clinician review adverse event information received from online assessments on a weekly basis. The site PM will be asked to follow up with any participant who reports an adverse event to ascertain whether or not the event resulted in hospitalization or appeared to be an unexpected reaction or side effect from the study intervention. The lead PM facilitates the submission of any reportable adverse events to the respective IRBs, site medical monitor, and/or the Data and Safety Monitoring Committee (DSMC). Events not meeting the criteria for immediate reporting are submitted to the IRBs at the time of continuing review.

Each military study site has a medical monitor assigned to the study. The medical monitor is responsible for reviewing adverse events, as well as unanticipated events that may increase the risk to trial participants, any related serious adverse event, or related participant death. Events meeting these criteria are also submitted to the DSMC and the U.S. Army Medical Research and Material Command, Human Research Protection Office.

### Study limitations

Given the nature of this trial, it is not possible to blind either the treating clinicians or participants to treatment assignment. This is an important limitation to this study. However, all participants, clinicians, and study personnel are blinded to next treatment assignment, and all key study personnel and data analysts are blinded to group assignment. One could also argue that the pragmatic nature of this comparative effectiveness trial is a limitation given the resulting lack of homogeneity in treatment approach both within and across groups. The advantage of this approach is that the results are more applicable to “real world practice”; the disadvantage is that one must sacrifice the homogeneity inherent within an RCT.

We believe that a comparative effectiveness design is the best way to answer questions that will be meaningful to policy makers as they consider the appropriate role for chiropractic care in active duty military populations. Further, our experience in the conduct of clinical trials in MTFs has shown us that this type of trial is feasible to conduct in busy clinical practice settings. We will address this limitation by collecting detailed data on the treatments rendered to participants, for both analysis and reporting purposes.

## Discussion

Since LBP is one of the leading causes of disability among U.S. military personnel, it is important to find pragmatic and conservative treatments that will not only treat LBP, but could ultimately preserve low back function so that military readiness is maintained. In this trial, we will evaluate the effects of the addition of chiropractic care to UMC on LBP pain and disability. A pilot study compared chiropractic care plus standard medical care with standard medical care alone for active duty military personnel with acute LBP [28]. Improvements in pain and disability were significantly greater in the chiropractic care group. This comparative effectiveness study will evaluate whether these prior findings can be reproduced in a larger sample, across multiple sites, and with varied populations including individuals with subacute and chronic LBP. The information gleaned from this large, multisite trial may assist military healthcare providers to more effectively treat a highly prevalent condition responsible for high healthcare costs, debilitating effects on patients, and military readiness.

### Trial status

Recruitment began in September of 2012. As of November 20, 2015, 750/750 participants were allocated and recruitment was closed.

## Abbreviations

ACT: Assessment of Chiropractic Treatment
CRADA: Cooperative Research and Development Agreement
DC: Doctor of Chiropractic
DoD: Department of Defense
DSMC: Data and Safety Monitoring Committee
IRB: Institutional Review Board
LBP: low back pain
MTF: Military Treatment Facility
NHP: Naval Hospital Pensacola
NMCSD: Naval Medical Center San Diego
NRS: Numeric Rating Scale
PCCR: Palmer Center for Chiropractic Research
PI: Principal Investigator
PM: Project Manager
PRO: patient-reported outcome
PROMIS: Patient Reported Outcomes Measurement Information System
RCT: randomized controlled trial
RMDQ: Roland-Morris Disability Questionnaire
SQL: Structured Query Language
SSL: Secure Socket Layers
STaRS: Submission Tracking and Reporting System
UMC: usual medical care
WRNMMC: Walter Reed National Military Medical Center
